### Screening, Recruitment, and Enrollment

Before their scheduled primary care visit, all eligible patients received a web-based or text link to a web-based SIS to complete. CRIs attempted to contact patients who had not completed the SIS on the web up to 3 times and completed the screener with them by phone if they were reached. Patients who screened at risk through the web-based SIS or through CRI contact and were randomized to the STEADI arm depending on the provider they were seeing were asked if they had (1) a computer, tablet, or phone with a camera and internet—if not, if they could participate by phone; (2) a clear hallway and corner in their home with space to assess gait or balance; and (3) someone nearby they could call upon for help if needed during the assessment. Those patients who answered yes to all 3 questions were then asked to provide informed consent to participate in the study. Patients who consented were asked if they had a blood pressure cuff at home (if not, the CRI ordered a cuff to be sent to their address), scheduled for a preassessment technology and home set-up call, and scheduled for a STEADI assessment before the primary care visit. Patients received an email with study information and instructions outlining the assessment process. Patients who were reached but did not consent to study inclusion were offered and provided STEADI assessments, although their data were not transmitted to the analytic team and were not included in analyses. Patients who were not reached were not included in analyses.

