**Methods:**

STEADI Options was a pragmatic RQIT implemented within a health system comparing a telemedicine version of the STEADI fall risk assessment to the standard of care (SOC). Before screening, we randomized all eligible patients in participating clinics into the STEADI arm or SOC arm based on their scheduled provider. All received the Stay Independent screener (SIS) to determine fall risk. Patients were considered at risk for falls if they scored 4 or more on the SIS or answered affirmatively to any 1 of the 3 key questions within the SIS. Patients screened at risk for falls and randomized to the STEADI arm were offered a registered nurse (RN)–led STEADI assessment through telemedicine; the RN provided assessment results and recommendations to the providers, who were advised to discuss fall-prevention strategies with their patients. Patients screened at risk for falls and randomized to the SOC arm were asked to participate in study data collection only. Data on recruitment, STEADI assessments, use of recommended prevention services, medications, and fall occurrences were collected using electronic health records and patient surveys. Using staff time diaries and administrative records, the study prospectively collected data on STEADI implementation costs and all-cause outpatient and inpatient charges incurred over the year following enrollment.

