### Study Eligibility

Patients aged 65 years or older with a nonacute outpatient visit scheduled at participating primary care clinics were eligible for screening. Patients completed the SIS, and those with an SIS score of 4 or higher or those who answered “Yes” to any of the statements used as proxy to the 3 key questions within the SIS were eligible for enrollment (Textbox 1) [9]. Patients needed to be cognitively able to participate in the assessment, be able to converse in English, and have access to an able-bodied person to help with or respond to an emergency during the STEADI gait and balance assessments conducted by telemedicine (Textbox 1). Patients without valid phone numbers and those who opted out of receiving health system text messaging were excluded.

Stopping Elderly Accidents, Deaths, and Injuries (STEADI) Options trial patient eligibility criteria, Emory Health Services, 2020-2021.
**Patients aged 65 years or older with a qualifying (ie, nonacute) visit scheduled at 1 of the 5 designated Emory clinic implementation sites and:**
Identified as high risk for falls through the Stay Independent screener by scoring 4 or more or answering affirmatively to any of the following statements in the Stay Independent screener as proxy to the 3 key questions:Sometimes I feel unsteady when I am walking.I am worried about falling.I have fallen in the past year.Able to participate in the STEADI assessments:Cognitively able to answer screening questions and participate in assessment.English-speaking.Have a computer, tablet, phone with internet and a webcam, or telephone.Have an able-bodied helper who can be available to help or called for help during the STEADI gait and balance assessment (in case of unsteadiness or a fall).

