### Evaluation

We will analyze process outcomes, short- and long-term outcomes, costs, and cost-effectiveness of the implementation (Multimedia Appendix 6). Process analyses will evaluate the extent to which assessments were conducted through phone or Zoom calls, evaluated intended risk factors, and identified risks among participants who were assessed. Qualitative interviews with providers will be thematically analyzed to provide details on whether the intervention was implemented as intended and provide additional information on intervention feasibility, communication between implementation staff, perceived efficacy, and patient engagement.

Using an intent-to-treat approach, we will evaluate sample balance and assess short- and long-term outcomes comparing the STEADI and SOC arms. We will use survey and EHR data to evaluate differences between the arms in the short-term outcomes of (1) STEADI-indicated service use (eg, physical therapy and occupational therapy) and (2) prescriptions for medications that increase fall risks. For the long-term outcomes of (1) medically treated and self-reported falls and (2) all-cause health care costs from the Emory Healthcare system, we will use EHR data and administrative cost data. We will use the *International Classification Definition, 10th Revision, Clinical Modification* (ICD-10-CM) codes (Multimedia Appendix 2) and chart text notes to identify medically treated falls at Emory. Preliminary analyses indicate that ICD-10-CM codes without text note review are insufficient to differentiate individual fall episodes or determine fall severity. Therefore, we will also use self-report of falling with treatment at Emory to guide additional text note reviews for fall events that may not have been coded in the EHR. Falls will be coded as EHR-confirmed, self-reported medically treated falls outside the Emory system (EHR not confirmed), and self-reported and not medically treated to support analyses. We will additionally evaluate the impact of STEADI using a per protocol approach using a 2-stage residual inclusion approach.

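### A three-question gate before consent is described only for patients already assigned to STEADI, so the enrolled-only comparison is not intent-to-treat and assignment is not a clean instrument

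*Protocol article*

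**What the plan says.** All references are to the protocol article.

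- Order of events (Abstract, Methods): "Before screening, we randomized all eligible patients in participating clinics into the STEADI arm or SOC arm based on their scheduled provider".
- STEADI recruitment (Screening, Recruitment, and Enrollment): patients who screened at risk and "were randomized to the STEADI arm depending on the provider they were seeing were asked if they had (1) a computer, tablet, or phone" were also asked about "a clear hallway and corner in their home with space to assess gait or balance" and about someone nearby to call on. Then: "Those patients who answered yes to all 3 questions were then asked to provide informed consent to participate in the study".
- SOC recruitment (Abstract, Methods): "Patients screened at risk for falls and randomized to the SOC arm were asked to participate in study data collection only". No three-question step is described for this arm.
- General eligibility (Study Eligibility and Textbox 1): a device or telephone is required, and patients had to "have access to an able-bodied person to help with or respond to an emergency during the STEADI gait and balance assessments". Neither item refers to arm. Clear space at home is not listed.
- Losses after assignment (Screening, Recruitment, and Enrollment): reached patients who did not consent could have the assessment, but their data are left out. In addition, "Patients who were not reached were not included in analyses".
- Analysis (Evaluation): "Using an intent-to-treat approach, we will evaluate sample balance and assess short- and long-term outcomes comparing the STEADI and SOC arms". Statistical Procedures adds a per-protocol estimate with assignment as the instrument.

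**The concern.** Intent-to-treat takes its validity from comparing everyone as randomized. Here the arm was fixed first, and a filter described for one arm then decided who could be asked to enrol. Home space and a nearby helper could plausibly be related to fall risk. If they are, the enrolled STEADI patients differ from the enrolled SOC patients before any assessment takes place. Consent was also sought with different offers in the two arms (an assessment plus data collection, or data collection alone), which is a second route to different selection.

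All planned contrasts are exposed: falls, service use, prescriptions and costs. The instrumental-variable estimate is exposed too, because among enrolled patients assignment may be associated with home circumstances that influence falls. The Limitations section does not mention arm-specific selection. Where it states the direction of a bias, the direction is toward the null.

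**Working it through.** **1. The plan's own figures.** Sample Size Estimation gives a control risk of 0.50, a design effect of 1.05 and 80% power for RR 0.82, 0.78 and 0.75 at 500, 350 and 250 per arm. Alpha is not stated; two-sided 0.05 is assumed. With n/1.05 per arm and a pooled-variance test of two proportions, power is 79.7%, 81.7% and 78.7%. The stated figures reproduce, so RR 0.78 at 350 per arm is a fair yardstick.

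**2. Which gate items are specific to STEADI.**

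| Item | General eligibility list | Pre-consent gate described for STEADI |
|---|---|---|
| Device or telephone | yes, no arm named | yes |
| Helper | yes, no arm named | yes |
| Clear hallway and corner | no | yes |

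The article does not say that any of the three was checked in SOC patients.

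**3. Apparent effect when there is none.** Let f be the share of at-risk patients failing the gate and r their fall risk. The documents give neither, so both are assumptions. If SOC is unfiltered with risk 0.50, the risk among those passing is p = (0.50 − f·r)/(1 − f), and the apparent RR is p/0.50. For example, f = 0.20 and r = 0.70 give p = (0.50 − 0.14)/0.80 = 0.45 and RR 0.90.

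The chance of a false significant benefit is Φ[(d − 1.96·s0)/s1]. Here d = 0.50 − p, s0 and s1 are the pooled and unpooled standard errors, and the effective sizes are 353/1.05 = 336.2 and 307/1.05 = 292.4. In the example d = 0.05 and s0 = s1 = 0.0399, so (0.05 − 0.0782)/0.0399 = −0.71, which gives 24%. False harm uses −d.

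| f | r | p | Apparent RR | False benefit | False harm |
|---|---|---|---|---|---|
| any | 0.50 | 0.500 | 1.00 | 2.5% | 2.5% |
| 10% | 0.60 | 0.489 | 0.98 | 4.6% | 1.3% |
| 10% | 0.70 | 0.478 | 0.96 | 8.0% | 0.6% |
| 20% | 0.60 | 0.475 | 0.95 | 9.1% | 0.5% |
| 20% | 0.70 | 0.450 | 0.90 | 24% | 0.1% |
| 20% | 0.40 | 0.525 | 1.05 | 0.5% | 9.1% |

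**4. What enrolment can tell.** Results gives 307 STEADI and 353 SOC, 660 in all. Against 50:50, z = (307 − 330)/√165 = −1.79, p = 0.07.

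Randomization describes 3 weeks of SOC only and 6 weeks at 2:1. The enrolment period of 487 days is 69.57 weeks. With even weekly enrolment (assumed), the expected STEADI share is (60.57 × 0.5 + 6 × 2/3)/69.57 = 34.29/69.57 = 0.493. Expected STEADI enrolment is then 325.3, and z = −1.42, p = 0.16.

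Given 353 in SOC and equal contact and consent rates (assumed), STEADI enrolment would be about 343 with no gate, 343 × 0.9 = 309 at f = 10%, 274 at 20% and 240 at 30%. The observed 307 sits near 10%. Treating patients as independent, 20% is about 1.4 standard errors away and 30% about 3. Allocation was by provider-week, so these distances and p-values overstate the evidence.

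**The case against.** A reader might infer three stronger things, none of which the article supports.

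- **That only STEADI patients had to meet all three conditions.** Study Eligibility lists the device and helper items for everyone. The SOC enrolment steps are not spelled out, and the workflow figure is not available here. On the text, only the clear-space item is specific to STEADI. The device item can exclude very few people, since a telephone suffices and patients without a valid phone number were already excluded.
- **That the bias favours STEADI.** No fall risk is given for patients who fail the gate. Equal risk means no bias, and lower risk reverses it.
- **That most of the target effect could be artefact.** With 30% failing at risk 0.70, the RR would be (0.50 − 0.21)/0.70/0.50 = 0.83. But 30% fits 307 v 353 poorly unless STEADI patients were easier to reach or consented more often, which is not documented. The enrolment imbalance itself proves nothing.

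The plan also has partial safeguards: balance checks, prior-year records and costs, and adjustment for unbalanced covariates. These help with measured differences. They cannot be relied on for home space or helper access, which the article does not describe recording in SOC patients. Nor are all listed limitations said to bias toward the null: record loss and survey nonresponse carry no stated direction.

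What remains is enough for the point. At least one item is described for one arm only, after assignment, and patients not reached or not consenting are also dropped.

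**Conclusion.** The point holds in a limited form. As described, the analysis compares enrolled patients by assigned arm. It is not intent-to-treat, and the instrument inherits the same weakness. Sections Study Eligibility and Screening, Recruitment, and Enrollment do not agree on who had to meet which condition and must be reconciled.

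Over an assumed 10-20% failing with fall risk 0.60-0.70, the apparent RR under no effect is about 0.98 to 0.90, against a planned detectable RR of 0.78 at 350 per arm. The chance of a false benefit is about 5% to 24% instead of 2.5%. These figures rest on SOC risk 0.50, an unfiltered SOC arm, equal contact and consent, and two-sided alpha 0.05. If SOC patients were held to the same three questions, the gate itself would cause no bias; non-contact and different consent offers would remain. The existence of the selection step is clear from the text. Its size and direction are not.

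**What to change.** Enrolment has closed, and the article reports analysis complete with results unpublished. The changes are therefore to reporting and to added analyses.

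1. State whether SOC patients were asked the same three questions, and bring the two sections into agreement.
2. Report by arm the numbers assigned, screened at risk, failing each question, not reached and declining.
3. Describe the main comparison as one of enrolled patients by assigned arm, without the unqualified intent-to-treat label. Qualify the instrumental-variable estimate in the same way. List arm-specific selection, direction unknown, as a limitation.
4. Add a sensitivity analysis over the share failing and their relative fall risk, including values below 1, with adjustment for screener items, age, clinic and prior-year record data. Weighting enrollees alone is not a substitute: patients who fail the gate have zero probability of enrolment in STEADI.
5. Where permission allows, have the health system compare costs, prescriptions and record-coded falls in all screened-at-risk patients by assigned arm, as the intent-to-treat check. The planned fall outcome cannot be used there, because self-report guides part of the chart review and non-enrolled patients have no survey. The Evaluation section itself calls codes without note review insufficient, so the falls part of this check is weaker.

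The cost is some extra analysis, one further extraction if permitted, and a less favourable label. No new patients are needed.

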### Preassessment Technology and Home Set-Up Call

A total of 2 days before the STEADI assessment, CRIs called each patient and provided setup instructions based on a script. CRIs confirmed the patient had a stable internet connection and was able to start the videoconferencing software (Zoom; Zoom Video Communications). They asked the patient to use tape to mark 5 feet of space from their video call device for the visual acuity test and to mark a 10-foot path for the Timed Up and Go (TUG) physical therapy assessment. CRIs also had patients choose a safe corner of their homes for the modified 4-Stage Balance physical therapy assessment and ensured that the patient had an appropriate chair and wall space to set the chair against for the 30-Second Chair Stand physical therapy assessment. CRIs presented demonstration videos of STEADI’s 3 physical therapy assessments and helped patients adjust camera angles. Those patients scheduled for phone assessments were reminded of the scheduled assessment visit and given information regarding what to expect.

### STEADI Assessments

#### Overview

During the subsequent assessment call, the RN conducted 6 standardized assessments to identify the patient’s risk factors for falls. The protocol prioritized video calls but allowed for phone assessments for those unable or unwilling to participate in video assessments. Summaries of each assessment component, possible component findings, intended recommendations and interventions, and adaptations for phone assessments are described below and in table form (Multimedia Appendix 1).

#### Comorbidity Review

Before the assessment, the RN reviewed the patient’s EHR problem list for diagnoses of 6 comorbidities (Multimedia Appendix 2) associated with fall risk: cognition problems, Parkinson disease, cardiac arrhythmia, depression, or urinary incontinence [16,17]. Comorbidities were shared with providers in the RN’s recommendation statement.

#### Medication Review

Before the assessment, the RN reviewed the patient’s EHR medication list for any prescriptions from 10 classes of medications known to increase fall risk based on the Beers criteria (Multimedia Appendix 3) [18]. The RN additionally checked for polypharmacy, most commonly defined as prescriptions for 5 or more medications [19]. During the assessment, the RN confirmed with the patient the accuracy of the prescriptions listed in the EHR. The RN reported medication-related fall risk in her or his report for the provider and provided medication management educational materials to the patient (Multimedia Appendix 4). The RN also shared a recommendation to assess and adjust medications considered to increase risk of falls with providers.

#### Falls History

The RN asked how many times the patient had fallen in the past 12 months. If the patient reported a fall within the past 12 months, the RN asked if the patient sought medical attention for any fall or experienced loss of consciousness or broken or fractured bone or bones resulting from a fall. Fall history information was added to the provider report to increase the salience of fall prevention information.

#### Assessment of Feet or Footwear and Diabetes Assessment

The RN observed (through video) or asked about the patient’s current footwear, asked about foot pain or loss of sensation, and when applicable noted a diabetes diagnosis. Patient reports of foot pain, loss of sensation, or diabetes resulted in a RN note to the provider to examine the patient’s feet and the potential need for a referral to podiatry. The RN also reviewed a safe footwear handout (Multimedia Appendix 4) with all patients and emailed it to patients following the call.

#### Assessment of Visual Acuity

The RN projected the Banner eye chart on Zoom for the patient to read with their contact lenses or eyeglasses from five feet away (the distance was marked during the technology set up call) for both eyes together and each eye individually [20]. Phone patients were asked to self-report any vision problems. If the video screening or self-report indicated vision problems, the RN noted the result and recommended an eye health referral.

#### Gait and Balance

For video patients, the RN conducted the 30-Second Chair Stand test, the TUG, and the first three stages of CDC’s 4-Stage Balance Test [21-23]. During the 30-Second Chair Stand test, the RN counted the number of times in 30 seconds the patient rose to a full standing position from sitting in a chair without using their hands. For the TUG test, the RN timed how long it took a patient to stand up from their chair, walk 10 feet, turn around, walk back to their chair, and sit down. During the balance test, the RN observed the patient in 3 progressively difficult standing positions: (1) feet side-by-side, (2) one foot touching the big toe of the other foot, and (3) one foot in front of the other, heel touching toe. Patients assessed by phone without video were asked 10 questions (Multimedia Appendix 1) that corresponded with the physical domains tested by the 30 Second Chair Test, TUG, and the first three stages of 4-Stage Balance Test.

If a patient failed any of the mobility tests, exhibited signs of unstable gait, or reported difficulties, the RN discontinued gait and balance assessments and recommended physical therapy referral through the provider messaging center. With the increased popularity of fitness programs for older adults [24], the RN recommended a web-based tai chi for arthritis program (Multimedia Appendix 4) for patients that passed all 3 tests, as all patients were still considered to be at risk for falls based on the SIS [25].

#### Orthostatic Hypotension

The RNs evaluated observed changes in systolic blood pressure by measuring sit-to-standing blood pressure. Sit-to-standing was chosen over a supine-to-standing test to increase feasibility for in-home assessment [26]. The patient measured their blood pressure using their own cuff or one provided by the study and sat for at least 2 minutes before standing. Patients experiencing a systolic blood pressure drop of more than 15 mm Hg when standing from their chair were given STEADI-based educational materials on managing orthostatic hypotension (Multimedia Appendix 4), and the RN reported the finding to the provider for management [27]. The RN also asked the patient about dizziness and relayed any reports of dizziness to the provider.

#### Home Safety Risks

The RN reviewed the CDC brochure *Check for Safety: A Home Fall Prevention Checklist for Older Adults* (Multimedia Appendix 4) with each patient [28]. *Check for Safety* asks 17 questions about the home’s floors, stairs and steps, kitchen, bathrooms, and bedrooms and suggests ideas for removing or reducing fall hazards. The RN communicated home safety risks and a recommendation for occupational therapy to the provider for indicated patients.

#### Vitamin D Deficiency

Vitamin D deficiency is common and often underdiagnosed among older adults, although recommendations on supplementation are mixed [29]. The RN asked the patient if they usually take a vitamin D supplement with their other medications. If the patient did not take a vitamin D supplement, the RN recommended the provider check vitamin D levels and consider supplementation if vitamin D levels were less than 20 ng/ml.

#### RN Recommendations and Provider Action

The RN reviewed health education materials with the patient and sent these materials in an email follow up. RNs compiled assessment results, the educational materials presented to the patient, and their recommendations for referrals and care management and entered them into the patient’s EHR and sent assessment results and recommendations to the provider using the EHR messaging center. Providers in each participating clinic were informed about the study protocol, communication methods, and actions they could take to act on information contained in the RN report. Provider actions included ordering patient referrals to physical therapy, optometry, podiatry, the neurovestibular clinic (ie, dizzy clinic), and occupational therapy; reviewing and changing patient medications when indicated; and testing patients for vitamin D levels. Providers acted on RN recommendations at their clinical discretion (Multimedia Appendix 5). For example, at the patient’s upcoming primary care visit, providers would evaluate whether the medications identified by the RN should be adjusted or if a referral to Emory’s Dizziness and Balance Center and providing the Epley maneuver home exercise handout was warranted [30].

